### 2.6. Interventions

The ACE operation in this study will be carried out in accordance with the Acupuncture Technical Operation Standard of the People’s Republic of China for ACE. Participants in both groups will accept treatments once every 2 weeks, for an 8-week period. During treatment, participants will be separated in different treatment rooms to avoid communication. Both treatments will be conducted by trained acupuncturists who are qualified, have acupuncture affiliation, and experience in clinical practice for more than 3 years. During the treatment and observation period of the study, if the participant’s pain symptoms worsen, the oral NSAIDs drug celecoxib (Pfizer Pharmaceuticals Ltd.) (Frampton and Keating, 2007; Foster et al., 2018) will be given orally for 2 days at a dose of 200 mg twice daily. If pain remains unrelieved, participants will be withdrawn from the study.

#### 2.6.1. Intervention group

(1)**Acupoints:** According to the theory of TCM and previous clinical practice experience, this study will select the bilateral acupoints of Shenshu (BL23) and Dachangshu (BL25). The position and depth of acupoints for needle insertion are in accordance with the Name and Location of Acupoints (GB/T12346-2006), a standard of The People’s Republic of China. Details of selected acupoints are shown in Table 1 and Figure 2.(2)**Preparation of ACE:** The main instruments utilized in the ACE treatment operation include an embedding needle, combinating of needle tubing and liner core, and absorbable surgical chromic catgut (Yangzhou Longhu Medical Instrument Co., Ltd., Yangzhou City, Jiangsu Province, China), all of which are disposable sterile products. The embedding needle is shown in Figure 3. Participants will stay in the prone position during the operation process.(3)**Operation procedures:** Firstly, the skin of the target acupoint region will be exposed and sterilized with iodophor. After disinfecting hands and wearing sterile gloves, the acupuncturists will cut the absorbable surgical chromic catguts into 1 cm long pieces, and place the small catgut into the pinpoint of the embedding needle tubing, where the liner core will be moved up 1 cm. Then, acupuncturist will use the thumb and index fingers to fix the acupoint, while, with the other hand, inserting the needle perpendicularly to the skin surface of the acupoint at a depth of approximately 1 cm. Secondly, acupuncturists will apply lifting, inserting, and twisting techniques to stimulate special sensations, presenting soreness, such as numbness, swelling, or radiation, but no pain, which are described as *Deqi* in TCM theory. Thirdly, by pressing down the liner core of the embedding needle, the catgut in the needle tubing will be embedded in the muscle layer. Finally, both the liner core and needle tubing will be pulled out of the acupoint, and the post-treatment acupoint will be covered by a cotton ball with tape for 24 h.

**TABLE 1 T1:** Locations of acupoints in the study.

	Acupoints	
	BL23 Bladder meridian	BL25 Bladder meridian
Needle insertion	On the lumbar region, on the same level of the second subspinous of the lumbar vertebra, and 1.5 cun lateral to the posterior midline.	On the lumbar region, on the same level of the fourth subspinous of the lumbar vertebra, and 1.5 cun lateral to the posterior midline.
Major indication and actions	Bone problems, low back pain, difficulty in urination, oedema	Pain in lumbar region and lower extremities.
Manipulation	Insert the needle 1.0 cm perpendicularly	Insert the needle 1.0 cm perpendicularly

**FIGURE 2 F2:**
[figure not shown]
Locations of acupoints.

**FIGURE 3 F3:**
[figure not shown]
Parts of the acupoint catgut embedding device.

For the standard and safe operation of ACE, the acupuncturists should: (1) ensure that the operation of ACE is conducted in a strictly sterile surrounding; (2) avoid catguts being embedded in the adipose tissue, which may cause fat liquefaction; (3) ensure that the chromic catgut is fully embedded in the deep tissue, and will not be exposed to the skin surface; (4) grasp at an appropriate angle and depth of the operation, to avoid damage to internal organs, major blood vessels, and nerves; and (5) inform participants regarding the precautions after treatment, such as keeping the lumbar region away from water for 24 h.

#### 2.6.2. Control group

In the sham ACE group, the embedding needle and acupoints are the same as those of the intervention group, but no catgut will be placed into the needle tubing before being inserted into the acupoints, so that no catgut will be left under the tissue after the needle is pulled out. At the same time, the needle will be withdrawn immediately, because inserting to the acupoints at a depth of 1.0 cm without retaining the needle to activate the *qi*, which is essentially different from traditional acupuncture.

### 2.7. Outcomes measurement

The efficacy evaluation in this study will include the primary outcome indicator VAS (Bijur et al., 2001). The secondary outcomes are the Roland-Morris Disability questionnaire (RMDQ) (Law et al., 2021), Oswestry Disability Index (ODI) (Mehra et al., 2008), and the Short Form 36-Health Survey (SF-36) (Taft et al., 2004). Safety outcomes will be evaluated by the incidence of adverse event. All evaluation indicators will be assessed at six time points: baseline, mid-treatment (4 weeks of treatment), post-treatment (8 weeks of treatment), and 1 month, 3 months, and 6 months after the treatments. Researchers who do not take responsibility for other processes in the study will be appointed as outcome assessors. Details of the observational items and the time window for data collection are shown in Table 2.

**TABLE 2 T2:** Schedule of enrolment, interventions, and assessments.

	Enrolment and allocation		Treatment period				Follow-up period		
Timpepoint	Screening (−3 to 0 d)	Allocation (0 d)	2 w	4 w	6 w	8 w	1 m	3 m	6 m
**Enrollment**									
Vital signs	X		X	X	X	X			
Previous medical history	X								
Inclusion/exclusion assessment	X								
Informed consent	X								
Allocation		X							
**Interventions**									
ACE treatment		X	X	X	X	X			
sham ACE treatment		X	X	X	X	X			
**Assessments**									
VAS		X		X		X	X	X	X
ODI		X		X		X	X	X	X
RMDS		X		X		X	X	X	X
SF-36		X		X		X	X	X	X
Adverse events		X		X		X	X	X	X
Analysis of outcomes									X

d, day; w, week; m, month; ACE, acupoint catgut embedding; VAS, visual analog scale; RMDS, Roland Morris Disability Scale; ODI, Oswestry Disability Index; SF-36, the Short Form 36-Health Survey.

#### 2.7.1. Primary outcome

Visual analog scale will be used as the primary outcome to assess the intensity of CNLBP. Participants will be requested to measure their pain intensity on a 10-cm horizontal VAS, with 0 showing no pain and 10 showing the most severe pain.

#### 2.7.2. Secondary outcome

##### 2.7.2.1. The Roland-Morris Disability Questionnaire

Dysfunction of daily life caused by CNLBP will be assessed by the RMDQ, which contains 24 questions about the daily physical activities and function in daily life. Participants choose “yes” or “no” as the answer to each question, to describe their situations. The answer “yes” marks one score, with a total score ranging from 0 to 24, and the higher score reflecting more severe dysfunction.

##### 2.7.2.2. The Oswestry Disability Index

Oswestry Disability Index will be used to assess the disability in patients with CNLBP. The ODI consists of 10 items: pain, personal care, lifting, walking, sitting, standing, sleep, sex life, social life, and travel. The score for each question ranges from 0 to 5, according to the different degree from normal to severe. The total score will be worked out with a percentage, where the higher percentage means a more severe disability evaluation.

##### 2.7.2.3. The Short Form 36-Health Survey

Short Form 36-Health Survey is a general health measurement applied in populations with chronic diseases. It covers a systematic evaluation of physical and mental health with 8 domains (pain, physical functioning, role-physical, general health, vitality, role-emotional, mental health, and social functioning) covered by 36 questions. The score for each domain will be converted to a scale of 0–100, with higher scores indicating better quality of life.

#### 2.7.3. Safety assessment

Adverse events that happen during the study will be recorded in the CRFs in detail, including the time of occurrence, symptoms, duration, treatment methods, and outcomes. Adverse events will be assessed by the specialists in the panel, to determine whether the conditions are treatment related and whether further rescues are needed. Adverse events frequently occurring in ACE treatment include fainting, acupoint swelling, and subcutaneous hemorrhage, and will be addressed by symptomatic treatment methods. Once the adverse events are defined as severe, such as acupoints infection, allograft rejection, or major organ damage, the research process will be terminated and the inspectors of the monitoring panel will reveal the participant’s allocated intervention at once. Consequently, the participant will withdraw from the study and accept systemic treatments. The cost of treatments for adverse events arising from this study will be paid by the sponsor of this study. The monitoring panel will report the SAEs to the ethics committee, while the researchers will closely follow the participants’ condition, and record it in detail in the CRF.

### 2.8. Data collection and management

After the included participants sign the informed consent forms, researchers will collect individual information, such as general demographic information, clinical history, and baseline data for VAS, RMDQ, ODI, and SF-36. Outcome indicators will be measured at the previously indicated six time points, and documented in the CRFs. When the trial is completed, two researchers who are neither involved in the distribution nor the outcome evaluation will independently extract data from CRFs into an Excel table. The statistician will then conduct statistical analysis on this data after double check confirmation. To protect the privacy of participants, personal names will be replaced by numbers combined with initials. Researchers shall maintain data confidentiality for 5 years after the termination of the trial. In order to reduce the dropout rate of participants, researchers will contact the participants by telephone 2 days before their treatments to enquire on their conditions and encourage them to accept the treatments as scheduled.

### 2.9. Quality control

To achieve credibility and consistency in the study results, all researchers will receive standardized training in advance, including identification and allocation of eligible participants, treatment procedures, outcome evaluation, management of adverse events, and CRF completion. In addition, a data and safety monitoring panel consisting of three experts in different fields will be established, who are independent from the sponsor and have no conflict of interest with the study. The panel will conduct casual inspection to reduce potential biases in the study process and data analysis. Once any violation of the research requirements or SAEs are identified, the panel will notify the principal investigator, or suspend the study at any time.

### 2.10. Statistical analysis

Statistical analysis will be computed using Statistical Analysis System (SAS) v9.4 by a statistician. Continuous variables subject to normal distribution are expressed as mean ± standard deviation, otherwise they will be expressed as median (interquartile range). Discontinuous variables will be expressed as composition ratio and rate. The baseline comparison of continuous variables will be performed by *t*-test or non-parametric test, and the baseline comparison of discontinuous variables by the chi-squared test. Repeated measures analysis of variance (RM-ANOVA) will be performed on the measurement data at multiple observation time points, to analyze the trend over time and the interaction between treatment times. The statistical significance level will be 0.05 (bilateral) with 95% confidence interval. The safety analysis will mainly be based on descriptive statistics, including the incidence and the specific description of adverse events.

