### 2.5. Sample size

The VAS score is the primary outcome indicator for this trial. Based on the results of the pre-test, it is known that the VAS score in the control group was 4.64 ± 1.42 cm and is expected to be reduced by 1.02 cm after treatment with ACE, setting a two-sided test with α = 0.05, β = 0.10. A sample size of 34 cases per group was calculated using PASS 15 software. Considering the 20% lost to follow-up calculation, the final number of cases needed for at least two groups was 41, for a total of at least 82 participants included.

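### The trial is sized on one after-treatment VAS difference, but no primary visit is named and the only stated efficacy analysis, RM-ANOVA for trend and interaction, does not estimate that difference

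*Protocol article*

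**What the plan says.** Section 2.7.1 defines the primary outcome by instrument only: "Visual analog scale will be used as the primary outcome to assess the intensity of CNLBP". Section 2.7 gives the schedule: "All evaluation indicators will be assessed at six time points: baseline, mid-treatment (4 weeks of treatment), post-treatment (8 weeks of treatment", followed by 1, 3 and 6 months after treatment. That is five post-baseline assessments, and neither the text nor Table 2 marks one as primary.

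Section 2.5 works from one two-group comparison. In the pre-test "the VAS score in the control group was 4.64 ± 1.42 cm", and this "is expected to be reduced by 1.02 cm after treatment with ACE". The design values are "setting a two-sided test with α = 0.05, β = 0.10", and the result is "A sample size of 34 cases per group was calculated using PASS 15 software", raised to 41 per group for losses. The visit behind the 1.02 cm is not identified.

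Section 2.10 states one efficacy analysis: "Repeated measures analysis of variance (RM-ANOVA) will be performed on the measurement data at multiple observation time points, to analyze the trend over time"; the sentence then adds an interaction of treatment and time. On the error level it says only "The statistical significance level will be 0.05 (bilateral) with 95% confidence interval". The t-test in that section is reserved for comparing baseline characteristics. The section names no between-group contrast, no visit and no deciding F-test.

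**The concern.** Sample size and analysis should refer to the same quantity. Here section 2.5 uses the difference between two means at one time, and section 2.10 describes how means move over several times.

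- The time trend pools the arms and says nothing about treatment.
- The interaction is an omnibus test, with 5 degrees of freedom if all six visits are levels. A significant result shows neither when the arms differ nor in which direction.
- The group effect, which RM-ANOVA also yields but section 2.10 does not mention, averages the difference over all visits in the model.

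None of these returns an estimate of the 1.02 cm difference with its confidence interval. At stake are whether the trial has the power its size implies, and whether the primary conclusion could be drawn from a test or a visit chosen after the data are seen.

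**Working it through.** **Inputs from the article.** Difference 1.02 cm, SD 1.42 cm, two-sided α 0.05, β 0.10, 34 per group before losses (2.5); six assessments, five after baseline (2.7).

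**Assumptions, not in the article.** SD 1.42 at every visit; compound symmetry with correlation ρ = 0.3, 0.5 or 0.7; 34 evaluable per group; the effect profiles below.

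**The plan's own figure.** n = 2(SD/difference)²(z_α + z_β)².
- Two-sided: 2 × (1.42/1.02)² × (1.960 + 1.282)² = 40.7, so 41 per group (42 with the t distribution).
- One-sided: 2 × (1.42/1.02)² × (1.645 + 1.282)² = 33.2, so 34.

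The stated 34 therefore matches a one-sided test. That is a separate matter, but it sets the benchmark: with 34 per group the two-sided t-test has 83% power (89.5% with 41).

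**Formulas for k visits with between-group differences d_t.**
- Group effect: the mean of d_t, tested against SD × √[(1 + (k−1)ρ)/k] with a noncentral t.
- Interaction: noncentrality n Σ(d_t − mean)² / [2 SD²(1 − ρ)], on k−1 and (k−1)(2n−2) df.
- Baseline-adjusted week-8 contrast: 1.02 tested against SD × √(1 − ρ²).

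**Profiles** (baseline, 4 w, 8 w, 1 m, 3 m, 6 m).
- Fading: 0, 0.51, 1.02, 0.77, 0.51, 0.26. Mean 3.07/6 = 0.51; sum of squared deviations 0.650.
- Constant: 0, then 1.02 five times. Mean 5.10/6 = 0.85; sum of squared deviations 0.867.

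**Worked case, ρ = 0.5.** SD of a participant's six-visit mean: 1.42 × √(3.5/6) = 1.085. Interaction noncentrality, fading: 34 × 0.650/(2 × 2.016 × 0.5) = 11.0, giving 72% power.

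| Power with 34 per group | ρ 0.3 | ρ 0.5 | ρ 0.7 |
|---|---|---|---|
| Fading, six levels: group effect | 62% | 48% | 39% |
| Fading, six levels: interaction | 55% | 72% | 93% |
| Constant, six levels: group effect | 96% | 89% | 80% |
| Constant, six levels: interaction | 69% | 85% | 98% |
| Constant, baseline left out: group effect | 99% | 96% | 92% |
| Constant, baseline left out: interaction | 5% | 5% | 5% |
| Simple t-test at one visit | 83% | 83% | 83% |
| Week 8 adjusted for baseline VAS | 86% | 92% | 98% |

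The 5% row follows directly: with the same difference at all five visits, every d_t equals the mean, the noncentrality is zero and power equals α.

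**Error rate if the visit is open.** For five independent tests at 0.05, 1 − 0.95⁵ = 22.6%. Simulating five equicorrelated tests gives 21%, 18% and 15% at ρ = 0.3, 0.5 and 0.7. This applies only if any one visit may carry the claim.

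**The case against.** A reader might infer that RM-ANOVA loses power. The article does not support that as a general statement. With a constant effect and ρ = 0.5, the six-level group effect (89%) and interaction (85%) both exceed the simple t-test (83%). Averaging shrinks the difference to 0.85 cm, but it also shrinks the variance. Part of the advantage of the adjusted week-8 contrast comes from the covariate, so the comparison with the plan's own sizing is against 83%, not 86% to 98%. This stands: power may be lower or higher than planned, and what can be said is that it is not fixed.

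A reader might also infer that RM-ANOVA inflates the type I error. A single prespecified F-test holds 5% under sphericity. In simulation, an uncorrected interaction test reached 7.7% to 8.5% under first-order autoregressive correlation of 0.7 to 0.85. The 15% to 21% comes from leaving the visit open, and section 2.10 plans no visit-by-visit tests.

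That baseline is one of the RM-ANOVA levels is an inference from the six time points in section 2.7; section 2.10 does not say so. Leaving baseline out does not rescue the plan, as the 5% row shows.

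A conflict between RM-ANOVA and the intention-to-treat statement is tempting too, since the classical method needs complete rows. It is not shown: section 2.3.4 brings the last outcome data of dropouts into the analysis, so they need not be deleted.

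Finally, covariance structure and model terms can properly be left to an analysis plan. The primary visit and contrast are different in kind, because section 2.5 already relies on them.

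**Conclusion.** The point holds as a mismatch between stated elements. The sample size rests on one after-treatment difference, no visit is designated for it, and the stated efficacy analysis neither estimates nor directly tests it. The 90% power claimed in section 2.5 therefore cannot be attached to the planned analysis, and the test that decides the trial is undefined.

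The consequence is a range, not a fixed loss: group effect 39% to 99% and interaction 5% to 98% over the cases tabulated, against 83% for the comparison actually sized. The familywise risk of about 15% to 21% is conditional on a free choice among five visits.

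All power figures rest on assumed correlations, profiles and equal SDs. Section 2.3.2 restricts baseline VAS to between 4 and 7 cm, so baseline spread is probably below 1.42 (a uniform spread over 3 cm has SD 3/√12 = 0.87). The correlation with baseline may then be nearer the lower end, where adjustment gains least (86%). The mismatch itself depends on none of these assumptions.

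**What to change.** In sections 2.7.1 and 2.10, name the between-group VAS difference at week 8, the visit that section 2.7 labels post-treatment, as the single primary comparison at two-sided 0.05. Estimate it with baseline VAS as a covariate, either by ANCOVA at week 8 or as the week-8 contrast from a mixed model on the post-baseline visits. Choose one in advance, because the two treat missing outcomes differently. Report the difference with its 95% confidence interval. Make the other visits, and the RM-ANOVA trend and interaction, secondary. State in section 2.5 that the 1.02 cm refers to that visit.

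The cost is a few sentences and a few lines of SAS; baseline and week-8 VAS are already scheduled. The downside is that conclusions about durability at 1, 3 and 6 months become secondary. Section 2.12 reports that enrolment has begun, so the change should go through the amendment route in section 2.1 before any outcome data are analysed.

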### 2.11. Dissemination

Results of the study will be presented at scientific conferences and in peer-reviewed publications. Participants included in the study will also have the opportunity to obtain the study results by telephone or e-mail.

### 2.12. Trial status

Currently, the protocol is version 1.0, registered on 27 April 2022. At the time of protocol submission, potential participants of the study have been actively enrolled.

## 3. Discussion

Chronic non-specific low back pain, one of the most common conditions in orthopaedics, rehabilitation, and pain medicine, accounts for 1/3 (Wang et al., 2015) of daily outpatient visits, and is a major cause of increase in years of life lived with disability, in both developed and developing countries (Diseases and Injuries, 2020). Recently, evidence has been published for ACE being beneficial in relieving pain from patients (Jo et al., 2022). However, the evidence for clinical studies targeting ACE in CNLBP treatment is lacking. This trial is a single-center, prospective, randomized, patient-assessor-blinded, sham-controlled trial conducted in China, to evaluate the clinical efficacy and safety of ACE for CNLBP patients, and provide new ideas for the management of CNLBP.

Pain, a major symptom plaguing patients with CNLBP, is a subjective experience that can be influenced by physical, psychological, personal experience, social and cultural factors (Wijma et al., 2016; Reis et al., 2022). An accurate and objective assessment of pain is essential to evaluate the efficacy of ACE. The VAS, a simple scale consisting of a 10-centimeter horizontal line, is widely used as a tool for measuring pain (Grilo et al., 2007). Moreover, one of the advantages of the VAS is that its value changes continuously. On the one hand, it reflects the subtle changes in pain, and, on the other hand, continuous scores can be used for statistic parameter testing, which is recognized internationally and superior to non-parameter testing of the category assessment scale. As a result, VAS will be applied as the primary outcome in this study. The ODI and RMDQ scores will be used to further evaluate the mobility disorders of patients with CNLBP, so as to obtain a more objective evaluation for the ACE treatment. In addition, the SF-36 will be used to assess participants’ quality of life. Appropriate acupoints selection is an essential factor for ACE treatment. We will select Shenshu (BL23) and Dachangshu (BL25), which are common acupoints for the treatment of low back pain in clinical practice. Both acupoints are located in the lumbar region, and can be used to treat disorders on or near this certain part of the body, according to the theory of meridian in TCM; further, a previous study indicated that BL23 and BL25 could decrease VAS and RMDQ scores for patients with low back pain (Wang, 2018).

However, there are several limitations in this trial. Firstly, this study is a single-center trial, and the study population is mainly from southern China, meaning that the applicability of ACE in other regions will be not discussed. Secondly, due to the different occupations or living habits of different participants, we do not impose strict requirements on the daily life of participants apart from the clinic, which may affect the results of the study. Finally, the trial lacks a positive control group, to distinguish superiority or inferiority relative to the available treatments. Despite these potential limitations, the results of this trial are expected to provide evidence for the efficacy and safety of ACE in the treatment of CNLBP, which will be useful to doctors, stakeholders, patients, and researchers.

